## Methods

This is a case-control study where the patients with CLBP conditions and asymptomatic controls will be recruited from Thumbay Physical Therapy & Rehabilitation Hospital, Gulf Medical University, Ajman, United Arab Emirates. After obtaining ethical clearance, informed consent will be taken from all the recruited participants. The recruiting of participants for this study will be done from May 2022 to November 2022.

### Sample size

As for the calculation of the sample size, the odds ratio taken is 2 with the prevalence of 70% kinesiophobia [17] among CLBP patients and assumed the prevalence of 10% kinesiophobia among the controls, with the minimum required sample size of 600 [200 cases + 400 controls]. The case-control ratio taken is 1:2. The controls will be invited participants/patients who have no complaints of lower back pain at the Thumbay Physical Therapy & Rehabilitation Hospital, Ajman. All possible confounding factors will be controlled through subgroup analysis in later part during data analysis. The patients and controls will be identified from the outpatient clinic prospectively.

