## Abstract

**Background:**

Patients with chronic low back pain (CLBP) frequently present with kinesiophobia. Though large body of evidence reported the impact of kinesiophobia in patients with CLBP, there are paucity of studies in associating kinesiophobia to muscle endurance and position sense in patients with CLBP. The primary aim of the study is to compare the impact of kinesiophobia on lumbar extensor endurance, position sense in patient with CLBP, and asymptomatic individuals. Secondarily, we aim to examine the association between kinesiophobia and lumbar extensor endurance, position sense, pain intensity, and functional ability in patients with CLBP. Thirdly, we aim to assess the degree of association of various factors on CLBP, lumbar endurance, and position sense.

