**Discussion:**

The finding from this study can be generalized as this study has adequate sample size and subgroup analysis by adjusting the variables to draw a valid conclusion. The finding of this study will help the working physician to include assessment of kinesiophobia as part of musculoskeletal evaluation for patient with CLBP in a prospective diagnostic intervention.

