Kinesiophobia is described as an excessive, unreasonable, and crippling fear of performing a physical motion due to a feeling of vulnerability to a painful injury or reinjury [19]. Clinical studies suggest that an exaggerated negative cognitive response toward actual pain known as pain catastrophizing and fear of movement/(re)injury (kinesiophobia) is important in the etiology of chronic low back pain and associated disability [20]. These findings are consistent with a cognitive-behavioral perspective that underscores the importance of maladaptive interpretations of bodily sensations [20].

The mechanism can be described as follows: persons who catastrophically misinterpret innocuous bodily sensations, including pain, are likely to become fearful of pain, which results in at least two processes. First, pain-related fear is associated with avoidance behaviors and the avoidance of movement and physical activity in particular. Avoidance also means withdrawal from rewarding activities such as work, leisure, and family. Second, pain-related fear is associated with increased bodily awareness and pain hypervigilance. Hypervigilance, depression, and disuse are known to be associated with increased pain levels and hence might exacerbate the painful experience. This model is used to develop successful treatments [20–22].

Thus, kinesiophobia is correlated to pain-related interference and triggers motor activity changes that influence activities related to pain and pain-related disability management and control [18]. The prevalence of kinesiophobia in chronic pain varies from 50 to 70% [23]. A higher degree of kinesiophobia is correlated with higher levels of perceived pain [24] and lower level re-entry into pre-injury activities for all [CMP] chronic musculoskeletal pain conditions [25]. Thus, clinicians should consider kinesiophobia as an important factor in their preliminary assessment of patients with chronic LBP [18].

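### The three sample-size inputs cannot all hold (70% against 10% kinesiophobia is an odds ratio of 21, not 2), and 600 is not justified for the primary aim on endurance and position sense.

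*Protocol article*

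**What the plan says.** The Sample size section gives three inputs in one sentence: the "odds ratio taken is 2 with the prevalence of 70% kinesiophobia [17] among CLBP patients and assumed the prevalence of 10% kinesiophobia" among controls. The sentence ends "with the minimum required sample size of 600 [200 cases + 400 controls", and the next sets the ratio at 1:2. No alpha, sidedness or power is given, and no effect or standard deviation for endurance or position sense.

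The Background reports, for chronic pain generally: "The prevalence of kinesiophobia in chronic pain varies from 50 to 70" per cent.

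The abstract states the aim: "The primary aim of the study is to compare the impact of kinesiophobia on lumbar extensor endurance, position sense in patient with CLBP" and in asymptomatic people. The end of the Background repeats it. The abstract's methods paragraph says endurance and position sense will be compared between people with and without kinesiophobia. The Statistical analysis section adds comparisons of patients with controls, including on kinesiophobia itself.

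The abstract's discussion paragraph then concludes: "The finding from this study can be generalized as this study has adequate sample size". The main Discussion expects at least 80% of the planned sample to be available for analysis.

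**The concern.** An odds ratio and two prevalences are not three free choices, because two of them determine the third. If the stated three conflict, the reader cannot tell which were used or what effect the study was sized to detect.

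The second problem is the contrast. The inputs describe exposure prevalence in cases and controls. The primary aim asks how endurance and position sense relate to kinesiophobia. A size that suits the first question may be generous or thin for the second, depending on how many people with and without kinesiophobia fall in each group. The article nevertheless relies on the figure as a required minimum and as grounds for generalising.

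**Working it through.** **Inputs.** From the Sample size section: odds ratio (OR) 2; kinesiophobia prevalence p1 = 0.70 in cases and p0 = 0.10 in controls; r = 2 controls per case; 200 + 400. Assumed here because not stated: two-sided 5%, 80% power (z = 1.960 and 0.842, sum 2.80).

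**1. Coherence (needs no alpha or power).**
- 70% and 10%: OR = (0.7/0.3)/(0.1/0.9) = 21.0.
- OR 2 and 10% in controls: p1 = 2×0.10/(0.90 + 2×0.10) = 0.182.
- OR 2 and 70% in cases: odds in controls = (0.7/0.3)/2 = 1.167, so p0 = 1.167/2.167 = 0.538.
- The lower end of the Background range does not help: 50% against 10% gives OR = 1/(0.1/0.9) = 9.

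**2. Trying to reproduce 200 cases.** With p̄ = (p1 + r·p0)/(1 + r):
- Kelsey: n = (zα + zβ)² · p̄(1−p̄) · (r+1) / [r(p1−p0)²].
- Fleiss: n = [zα√((1+1/r)p̄(1−p̄)) + zβ√(p1(1−p1) + p0(1−p0)/r)]² / (p1−p0)², with or without continuity correction.

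| Pair kept | p1 v p0 | Kelsey | Fleiss | Fleiss, corrected |
|---|---|---|---|---|
| OR 2, 10% in controls | 18.2% v 10% | 196 | 205 | 223 |
| OR 2, 70% in cases | 70% v 53.8% | 109 | 107 | 116 |
| 70% and 10% | 70% v 10% | 7 | 7 | 9 |

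Worked example, first row, Kelsey: p̄ = 0.1273, so n = 7.85 × 0.1111 × 3/(2 × 0.0818²) = 195.3, rounded up to 196. At 200 + 400, power for 18.2% v 10% is 79%; at 160 + 320 it is 70%.

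Of the stated pairs, only the first comes near 200 cases at 80% power. It is not the only possible route once power is left open: OR 2 with 70% entered as the control prevalence (p1 = 1.4/1.7 = 82.4%) at 90% power gives 199 (Kelsey) or 200 (corrected Fleiss). That contradicts the stated 10% in controls, but it cannot be excluded as the origin of the figure.

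**3. What 200 + 400 offers for endurance and position sense.** Take 70%/10% and a continuous outcome in SD units. The cells with and without kinesiophobia are 140 and 60 (CLBP), 40 and 360 (controls), 180 and 420 (pooled). The detectable difference is 2.80 × √(sum of 1/n).
- Pooled, unadjusted: 2.80√(1/180 + 1/420) = 0.25 SD.
- Adjusted for case status: the information is 140×60/200 = 42 plus 40×360/400 = 36, total 78; 2.80/√78 = 0.32 SD.
- Within CLBP: 2.80√(1/140 + 1/60) = 0.43 SD.
- Within controls: 2.80√(1/40 + 1/360) = 0.47 SD.
- Difference in effect between groups: 2.80√(1/140 + 1/60 + 1/40 + 1/360) = 0.64 SD.

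If 80% are analysed (160 + 320, same prevalences), divide by √0.8 = 0.894: about 0.28, 0.35, 0.48, 0.52 and 0.71 SD in the same order.

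With 18.2%/10% instead, the CLBP cells are about 36 and 164. The detectable differences become 0.51 SD within CLBP and 0.69 SD between groups, while the control figure stays at 0.47 SD.

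**The case against.** Four points can be made for the plan.

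- **Six hundred is not shown to be too few.** It far exceeds what 70% against 10% needs, and it is about right for OR 2 with 10% in controls. This stands. A reader might infer that the study is underpowered, but nothing in the document supports that.
- **The origin of 600 is unknown.** A reader might infer from the table that the figure came from OR 2 with 10% in controls and that the cited 70% was never used. Without a stated alpha and power this cannot be asserted, because the 90%-power route above matches at least as closely. This stands as a limit on the diagnosis. The contradiction among the inputs is untouched, since it depends on neither alpha nor power.
- **The sized contrast is a planned one.** Kinesiophobia is to be compared between patients and controls, and factors associated with CLBP are the third aim. This stands, but that contrast is not the one labelled primary.
- **The primary aim can be read favourably.** The abstract's with/without comparison is not restricted to within-group or interaction tests, and pooled it detects 0.25 SD. The document names no interaction test, so 0.64 SD applies only if the aim is read as comparing the kinesiophobia effect between groups. This stands in part. On the protocol's prevalences, 140 of the 180 people with kinesiophobia would be cases (78%), against 60 of the 420 without (14%), so the pooled contrast is heavily mixed with case status and the adjusted 0.32 SD is the more useful figure.

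Further power work may exist in a document not shown. That would not repair the contradictory sentence in this one.

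**Conclusion.** Wrong as written. The three stated inputs are mutually impossible: the two prevalences imply an odds ratio of 21, more than ten times the stated 2. This follows from the article's own numbers without any assumption. Depending on which pair is kept, the requirement runs from about 7-9 to 196-223 cases, assuming two-sided 5%, 80% power and 1:2.

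The calculation addresses exposure prevalence in cases against controls, so neither the required-minimum label nor the adequacy claim is supported for the primary aim. For that aim, 200 + 400 would detect roughly 0.25 to 0.64 SD depending on the contrast, or 0.28 to 0.71 SD if 80% are analysed. These figures assume 70%/10% prevalence, continuous outcomes and 80% power. Whether they suffice depends on effects the article does not give.

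**What to change.** Keep 200 + 400 and rewrite the justification.

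1. State one coherent set of inputs with alpha, sidedness and power. Either keep 70% and 10% and give the implied odds ratio of 21, or keep odds ratio 2 with 10% in controls and give the implied 18.2% in cases (about 79% power at two-sided 5%). The second choice must be reconciled with the 50-70% reported in the Background.
2. State what 200 + 400 can detect for endurance and position sense, using the same prevalences as in step 1. Specify whether the primary contrast is pooled, adjusted for case status, within group, or a difference in effect between groups. Give the figure both for full data and for the 80% analysable share.
3. Limit the abstract's adequacy statement to the contrasts those figures support.

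The cost is wording only, with no extra participants. The drawback is that the stated precision will look less favourable for the within-group and between-group contrasts.

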### Inclusion criteria for CLBP subjects

Adults aged between 18 and 59 years [45].Patient suffering from low back pain for at least 3 months and referred by an orthopedic doctor or general physician.Participants with enough physical autonomy to take part in physical activities such as performing lumbar endurance and lumbar positioning test required of the study.

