### Exclusion criteria CLBP subjects

Low back pain patients with neurological deficit, any neurological disorder, post spinal fractures, history of spinal tumors, cauda equina syndrome, tuberculosis spine, any congenital spine anomalies, vestibular issue, joint instability in lower limb, cardiorespiratory problem, and hip arthritis.Patient under antidepressive medication and antihypertensive medicationPatient unwilling to participate

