### Inclusion criteria for asymptomatic subjects

Adults aged between 18 and 59 years.Either gender.

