### Exclusion criteria for asymptomatic subjects

History of (H/o) previous lower back injury.Participants with congenital spine anomalies, vestibular issue, joint instability in lower limb, cardiorespiratory problem, and hip arthritis.H/o inflammatory, infectious disease, and malignancy in the spinePatient under antidepressive medication and antihypertensive medication

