## Discussion

This study is to be conducted in Thumbay Physical Therapy & Rehabilitation Hospital which is equipped with all advanced equipment necessary for physiotherapy assessment associated with this study. Sample recruitment is expected to start from May 25, 2022, at Thumbay Physical Therapy & Rehabilitation Hospital, and Thumbay University Hospital and Gulf medical University, Ajman, United Arab Emirates.

Screening of individuals with and without chronic low back pain will be carried out by 4 experienced physiotherapists [2 males and 2 females] who are specialized in musculoskeletal and sports physiotherapy. In order to make the data collection uniform, all the therapists will be provided with the information about the study protocol including assessment methods using various assessment tools related to this study.

As per the medical record obtained on the prevalence of lower back pain conditions in Thumbay Physical Therapy & Rehabilitation Hospital and Thumbay University Hospital, we assume that the estimated sample size can be achieved within the study period given in the trial. Furthermore, the investigators of the study will contact the various departments of Thumbay University Hospital to refer the patients with and without low back pain to meet the sample required.

At least 80% of samples from the estimated sample size is anticipated for statistical analysis and reporting the study findings. Since the study covers a wide range of populations from various countries reporting to these medical centers, addressing confounding variables makes the study findings novel and generalizable.

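### Controls labelled 'asymptomatic' need only be free of low back complaints and previous back injury, so rehabilitation outpatients with other pain or neurological disease can qualify

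*Protocol article*

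**What the plan says.** **Source of controls.** The Sample size section states: "The controls will be invited participants/patients who have no complaints of lower back pain". It names the rehabilitation hospital as the place and continues: "The patients and controls will be identified from the outpatient clinic prospectively". The Discussion adds a second route, in which departments of the university hospital are asked to "refer the patients with and without low back pain to meet the sample required".

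**Control criteria.** Inclusion reads, in full: "Adults aged between 18 and 59 years.Either gender". Exclusions are previous lower back injury; "Participants with congenital spine anomalies, vestibular issue, joint instability in lower limb, cardiorespiratory problem, and hip arthritis"; inflammatory, infectious or malignant spine disease; and two drug classes.

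**Case criteria.** Exclusions begin: "Low back pain patients with neurological deficit, any neurological disorder". Inclusion also requires "Participants with enough physical autonomy to take part in physical activities", with the endurance and positioning tests given as examples. Neither requirement is on the control list.

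**Kinesiophobia figures.** The Background states: "The prevalence of kinesiophobia in chronic pain varies from 50 to 70% [23". The Sample size section takes 70% in cases and assumes 10% in controls.

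**The concern.** The comparison group is called asymptomatic throughout, including in the PECO statement, but the criteria make it symptom-free only in the low back. In a physiotherapy clinic, many people without back pain may be attending for pain elsewhere. The protocol's own Background figure suggests that those with chronic pain have kinesiophobia far more often than the assumed 10%.

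The unequal criteria bear on the measured outcomes. Position sense and extensor endurance are the outcomes of the primary aim, and the Background attributes proprioceptive deficits to impaired afference or its central processing. Excluding neurological disorder and requiring test ability in one group only means that the groups can differ on these outcomes for reasons unrelated to low back pain.

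At stake is the meaning of the case-control contrast. The estimate would depend on an unreported mix of clinic patients among the controls.

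**Working it through.** **1. The two lists side by side**

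| Criterion | Cases | Controls |
|---|---|---|
| Age 18–59 | yes | yes |
| Neurological deficit or disorder excluded | yes | no |
| Able to perform the tests | required | not stated |
| Previous lower back injury excluded | no | yes |
| Inflammatory spine disease excluded by name | no | yes |
| Spinal tumour or malignancy excluded | yes | yes |
| Spinal infection excluded | tuberculosis named | infectious disease named |
| Congenital spine anomaly, vestibular issue, lower-limb instability, cardiorespiratory problem, hip arthritis, two drug classes excluded | yes | yes |
| Pain at other sites excluded | no | no |

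There are two separate gaps. Some criteria differ between groups, in both directions. Pain at other sites is open in both lists, which matters for controls because they are called asymptomatic.

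**2. The plan's own contrast**

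Inputs (Sample size): 70% in cases, 10% in controls.

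OR = (0.70/0.30) / (0.10/0.90) = 2.333/0.1111 = 21.0; difference 60 percentage points.

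The section also names an odds ratio of 2, which these two prevalences do not give. That is a separate matter.

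**3. Effect of controls with other chronic pain**

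Let f be the share of controls with another chronic pain condition. The documents do not give f, so 10%, 20% and 50% are assumptions. Let q be kinesiophobia in that share: 50% or 70% (Background).

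Control prevalence = 0.10 × (1 − f) + q × f

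OR = 2.333 / [prevalence / (1 − prevalence)]

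| f | q | Control prevalence | OR | Difference (points) |
|---|---|---|---|---|
| 0 | – | 0.10 | 21.0 | 60 |
| 10% | 50% | 0.09 + 0.05 = 0.14 | 14.3 | 56 |
| 10% | 70% | 0.09 + 0.07 = 0.16 | 12.3 | 54 |
| 20% | 50% | 0.08 + 0.10 = 0.18 | 10.6 | 52 |
| 20% | 70% | 0.08 + 0.14 = 0.22 | 8.3 | 48 |
| 50% | 50% | 0.05 + 0.25 = 0.30 | 5.4 | 40 |
| 50% | 70% | 0.05 + 0.35 = 0.40 | 3.5 | 30 |

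With q above 10%, every f above zero moves the odds ratio toward 1.

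**4. Power**

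Take the worst row, 70% against 40%, with 200 cases and 400 controls. The standard error is √(0.21/200 + 0.24/400) = √0.00165 = 0.0406, and 0.30/0.0406 = 7.4. Power at a two-sided 5% level (assumed; none is stated) is above 99%. The damage is to the estimate, not to the chance of a significant result.

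**5. Endurance and position sense**

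The documents give no means, spreads or effects for these outcomes, so no size can be computed.

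**The case against.** **The control list is not simply looser.** Correct. It is stricter on previous back injury and on inflammatory spine disease, and both push the contrast away from the null. The net direction over all criteria is not determined. The expected pull toward the null is specific to kinesiophobia and to controls with other chronic pain.

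**Hospital controls are a recognised design.** Also correct. Taking both groups from one clinic is defensible, controls need not be patients, and referral from other departments widens the pool. Moving recruitment to staff or accompanying persons would be a trade-off, so a new control source is not required.

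**Excluding other pain in controls only creates a new asymmetry.** Partly stands. Cases could still have pain elsewhere. But the plan itself promises an asymptomatic comparator, and the definition only makes the criteria match that label.

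**A reader might infer that the bias is beyond repair.** The documents do not support this. The Procedures section has participants record pain area and associated symptoms and undergo a physical examination. If that covers controls, as the wording suggests, the comparison can be restricted afterwards. The planned subgroup analysis does not do this by itself: pain elsewhere and neurological disease are not among the factors described after the PECO model.

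**A reader might also infer that modest contamination erases the effect.** Starting from an odds ratio of 2 and 10% in controls, cases would be at 0.20/1.10 = 18.2%; 20% contamination at q = 50% puts controls at 18%, and the odds ratio near 1.0. But this sets patients with chronic low back pain at 18.2% beside other chronic pain patients at 50%. The documents give 70% for the former and 50–70% for the latter. The figure is a by-product of the conflict between the planning inputs, not evidence about contamination.

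**Conclusion.** The point holds. As written, the criteria admit people to the 'asymptomatic' group who have other musculoskeletal pain or a neurological disorder, and criteria relevant to the primary outcomes differ between groups.

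For kinesiophobia, the expected effect of controls with other chronic pain is attenuation. The size in the working rests on four things: 70% in cases, 10% in controls without such pain, 50–70% in controls with it, and an assumed share of such controls. The range is wide because that share is unknown.

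The documents do not support saying that every case-control difference shrinks: for endurance and position sense, a deficit among such controls is plausible, but no size or net direction can be given. The correlations within patients with chronic low back pain use no controls and are unaffected.

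**What to change.** 1. Apply the neurological-disorder exclusion, the test-ability requirement and the inflammatory spine exclusion to both groups.
2. Define 'asymptomatic' in the control criteria as no current musculoskeletal pain at any site. The Discussion expected recruitment from 25 May 2022 and the article is dated 6 June 2022, so some controls may already be enrolled. For these, use the pain area recorded under Procedures to restrict the primary case-control comparison to pain-free controls, and confirm that this item is completed for controls as well as cases.
3. Record the source of each control (rehabilitation outpatient clinic, referring department or other).

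The cost is an amendment to the eligibility wording and one extra field on the data form. The control pool becomes smaller, recruitment of the 400 is likely to be somewhat slower, and any enrolled control with other pain drops out of the primary comparison.

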### Procedures

The initial screening of participants will be performed by a physiotherapist (examiner 1) during the first physical therapy appointment. Then, the participants will be instructed to fill a Tampa Scale for kinesiophobia which is a questionnaire consisting of socio-demographic information (age, gender, weight, height), pain characteristics (pain area and associated symptoms); fear-avoidance behavior and physical examination carried out by the examiner. The evaluation of pain intensity and function will be performed through self-reported questionnaires (visual analog scale—VAS and Patient-specific Functional Scale). The physiotherapist (examiner 2) who carries out the lumbar endurance and position sense will be blinded for the cases and control group.

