### Statistical analysis

The statistical analysis will be computed using SPSS Statistics software, version 27 (IBM, Chicago, IL, USA). The data analyses will be conducted by a statistician. Continuous variables will be summarized using standard measures of central tendency and dispersion, either as mean and standard error, or median and interquartile range. Dichotomous or categorical variables will be summarized by frequencies or denominators and percentage.

Kinesiophobia, lumbar endurance, and joint position sense will be compared between patients and controls using appropriate statistical tools. Kinesiophobia scores will be correlated with lumbar extensor endurance and proprioception joint position errors, pain intensity, and functional ability. Chi-square test will be used to find the association between kinesiophobia and lumbar endurance and joint position sense. Spearman rank correlation will be used to find the correlation between kinesiophobia, pain, and functional ability. Simple and multiple binary logistic regression will be used to determine crude and adjusted odds ratio for kinesiophobia, lumbar position sense and kinesiophobia, and lumbar endurance.

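### Controls are not balanced to cases on age or sex, and the stated remedy, subgroup analysis, gives no adjusted overall patient-control difference in endurance or position sense

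*Protocol article*

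**What the plan says.** On who the controls are, Sample size in the protocol article says: "The controls will be invited participants/patients who have no complaints of lower back pain". The demographic criteria for asymptomatic subjects are "Adults aged between 18 and 59 years.Either gender". Cases have the same age limits ("Adults aged between 18 and 59 years [45") and must in addition be referred by an orthopedic doctor or general physician. The exclusions for controls are medical. The case-control ratio is 1:2, which sets a count and not a match. Sample size also says that both groups are identified prospectively from the outpatient clinic.

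On confounding, the sentence that follows the description of the controls reads: "All possible confounding factors will be controlled through subgroup analysis in later part during data analysis". No variables are named.

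On the comparison itself, Statistical analysis says: "Kinesiophobia, lumbar endurance, and joint position sense will be compared between patients and controls using appropriate statistical tools". The only adjusted model is described there as "Simple and multiple binary logistic regression will be used to determine crude and adjusted odds ratio for kinesiophobia, lumbar position sense", and likewise for kinesiophobia and endurance. It is not described as adjusting the patient-control difference.

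Age and gender are recorded for every participant (Procedures).

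**The concern.** The primary aim compares lumbar extensor endurance and position sense in people with chronic low back pain (CLBP) and asymptomatic people. Both are physical performance measures that may plausibly vary with age and sex. Cases arrive by referral and controls by invitation, with no step that makes their age or sex distributions alike. If the distributions differ, an unadjusted comparison mixes the effect of back pain with that of age or sex.

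With 600 people the standard error is small, so even a modest spurious difference can reach significance. The stated remedy does not solve this. Splitting the data into subgroups controls confounding within each subgroup but returns several imprecise comparisons and no single adjusted difference. The article rests its claims of validity and generalizability on having dealt with confounders (Abstract, Discussion), so the method used for this matters.

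**Working it through.** **The plan's own figure.** The document gives 200 cases and 400 controls, an odds ratio of 2 and a 10% prevalence of kinesiophobia in controls. Alpha and power are not stated; two-sided 5% and 80% are assumed here.
- Implied case prevalence: 2 × 0.10 / (1 + 0.10 × (2 − 1)) = 0.182.
- Two-proportion formula at 1:2: 205 + 410 (Fleiss, no continuity correction) or 196 + 392 (Kelsey). This is close to 200 + 400.
- The stated 70% prevalence in cases is not used in this reading, which is a separate matter. The calculation concerns a binary exposure and makes no allowance for age or sex.

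**Standard error of the unadjusted comparison, in SD units.**
- SE = √(1/200 + 1/400) = 0.0866.
- Detectable difference at 80% power: (1.960 + 0.842) × 0.0866 = 0.24 SD.

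**Effect of an imbalance.** The document gives no SD, age distribution, sex distribution or age slope, so these inputs are assumed.
- Spurious difference = slope per year × gap in mean age. A slope of 0.01 to 0.02 SD per year and a 10-year gap give 0.10 to 0.20 SD.
- A sex imbalance has the same form: 65% versus 45% of one sex, with a 0.5 SD sex effect, gives 0.20 × 0.5 = 0.10 SD.
- Rejection probability with no true difference = P(|Z + bias/SE| > 1.96):

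| Assumed spurious difference (SD) | bias/SE | Rejection of a nominal 5% test |
|---|---|---|
| 0.05 | 0.58 | 9% |
| 0.10 | 1.15 | 21% |
| 0.15 | 1.73 | 41% |
| 0.20 | 2.31 | 64% |

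The Discussion anticipates at least 80% of the sample in the analysis. At 160 and 320, SE = √(1/160 + 1/320) = 0.0968, and the range for 0.10 to 0.20 SD becomes 18% to 54%.

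**What subgroup analysis delivers.** Assume two sexes by four age bands, all equal.
- Per stratum: 200/8 = 25 cases and 400/8 = 50 controls.
- SE = √(1/25 + 1/50) = 0.245; detectable difference = 2.80 × 0.245 = 0.69 SD.

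**What a pooled, age-adjusted comparison delivers under a severe imbalance.** Assume cases split 15/25/30/30% and controls 60/20/12/8% over four age bands.
- Counts: 30/50/60/60 cases and 240/80/48/32 controls. Every band holds at least 30 cases and 32 controls.
- Information = Σ n₁n₀/(n₁ + n₀) = 26.7 + 30.8 + 26.7 + 20.9 = 105.0 (sum of unrounded terms).
- Balanced: 200 × 400/600 = 133.3. Ratio = 105.0/133.3 = 79%.
- SE = 1/√105.0 = 0.098, about 13% above 0.0866; detectable difference = 2.80 × 0.098 = 0.27 SD.

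Even under this severe split, one adjusted estimate detects 0.27 SD, against 0.69 SD in each separate stratum.

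**The case against.** **An unmatched design is accepted practice.** This stands. A case-control study without matching is sound if the comparison is adjusted and the groups overlap. Frequency matching would still need adjustment in the analysis, and it would stop age and sex being studied as factors for CLBP under the third aim. Lack of matching alone is not the defect.

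**The plan does intend to control confounding.** This also stands. Sample size says so, the Abstract couples subgroup analysis with adjusting variables, and adjusted odds ratios are planned. But the stated means is subgroup analysis, and the adjusted odds ratios are for kinesiophobia with position sense and with endurance. Neither yields an adjusted patient-control difference.

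**Covariate lists belong in an analysis plan that is not shown.** Fair, and the missing list is not the point. The point is the method that the article does state.

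**Stronger readings that the document does not support.** A reader might infer from recruitment at "Thumbay University Hospital and Gulf medical University, Ajman" that controls will be young campus volunteers. The Discussion names these places for sample recruitment in general, nothing mentions students, and Sample size identifies both groups from the outpatient clinic. A reader might also infer that later analysis could not repair an imbalance. The severe split above keeps 79% of the information and some overlap in every band, so adjustment would largely repair it. The rejection rates of 21% to 64% apply only if the comparison ignores age and sex altogether.

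**Conclusion.** The point holds as a weakness in how confounding is to be controlled. No step balances the groups on age or sex, the patient-control comparison is stated without adjustment, and subgroup analysis cannot supply an adjusted overall difference. The result can therefore be partly an age or sex difference.

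How large that part would be cannot be determined from the document. The 0.10 to 0.20 SD, the age slope and gap, the eight equal strata and the age-band splits are all assumptions used to show scale. What does not depend on them is that a named adjustment gives one pooled estimate from data already collected, which the stated approach does not. It is best treated as a free improvement; it does not show that the sampling is unsound or that matching is required.

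**What to change.** In Sample size and Statistical analysis, replace subgroup analysis as the means of controlling confounding with regression adjustment. Include age and sex as covariates in the patient-control comparisons:
- a linear model for hold time and for repositioning error;
- logistic regression where CLBP or kinesiophobia status is the outcome.

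Report the age and sex distribution of cases and controls so that readers can judge overlap. Subgroup results can stay as descriptive additions.

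The cost is two covariates already collected (Procedures) and one descriptive table. The total stays at 600, and the change can be made even if enrolment is complete, ideally before the data are analysed. If the groups turn out unbalanced, some precision is lost; in the severe assumed split the SE rises by about 13%.

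Frequency matching by age band and sex at enrolment is optional. It would protect overlap but may slow the filling of the last cells, and it gives up age and sex as CLBP factors under the third aim.
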